#### Data Safety Monitoring Board

The Data Safety Monitoring Board (DSMB) comprises at least 3 non-Investigator clinicians with expertise in interventional neuroradiology/neurosurgery that will review all adverse events occurring in the study according to the DSMB Charter. The DSMB will meet and review all clinical events continuously.

Any event meeting the definition of serious adverse event (SAE) must be adjudicated by the DSMB. The DSMB will also be provided with listings of all events and may choose to adjudicate events that are not serious in nature. Members may discuss any event with the investigator who was involved with the subject in question. The DSMB will use the same rating scale for relatedness. The DSMB adjudicated adverse events will be used in the analysis of the primary safety endpoint; DSMB will review and adjudicate the Medical Monitor’s categorization of event type and severity using the rating system previously referenced.

#### Frequency and plans for auditing trial conduct {23}

No scheduled auditing of trial conduct is planned. Upon request from the Swedish Medical Products Agency or its designees, all relevant trial documentation will be made available for audit.

#### Plans for communicating important protocol amendments to relevant parties (e.g., trial participants, ethical committees) {25}

The investigator should not implement changes to the protocol without prior approval by the sponsor and prior review and documented approval from the governing Ethics Committee and Competent Authority. The only exception to this requirement is the necessity to eliminate immediate hazards to subjects in the clinical investigation or when changes involve only administrative aspects (e.g., change in monitors, telephone numbers).

Any report of withdrawal of Ethics Committee or Competent Authority approval will be submitted to the sponsor. If significant changes in the implementation of the study or the study protocol (including research person information) are made after approval, an addendum must be written and sent by the principal investigator to the Ethical Review Authority for approval before this change can be implemented.

#### Dissemination plans {31a}

According to the Declaration of Helsinki, study results will be made publicly available as soon as possible after completion of studies and no later than 1 year after completion, regardless of whether results are positive, negative, or neutral, via publication and/or public database. The results, preliminary and final, may be presented at national and international meetings. The study is planned to be reported in scientific article/articles intended for an international peer reviewed journal.

This is an academically driven trial. Authorship and manuscript composition will reflect cooperation between the investigator, clinical investigation sites, and the sponsor. Authorship will be established prior to writing of the manuscript. No individual publications will be allowed prior to the completion of the final report for this clinical investigation. A publications committee will be formed to review and publish the data from the clinical investigation. This committee will consist of investigators and representatives of the coordinating site. The publications committee will write/review all drafts of abstracts, full-length manuscripts, and/or oral congress presentations/posters and will choose the appropriate journal (for manuscripts) or meetings (for abstracts) for submission.

The trial will start with recruitment of 30 participants. Data for this initial recruitment will serve as basis for interim analysis of inclusion rate and assessment of number of centers needed for study completion and may form basis for amendments to protocol. These first cases will be included in the final analysis.

## Discussion

The hypothesis of this trial is that endovascular treatment alone is safe and effective with a reduced reoperation rate compared to surgical evacuation in cSDH patients with clinical indication for surgical treatment.

The rationale for the trial design is the encouraging results with reduced reoperation rate for patients treated by endovascular embolization alone, where the reoperation rates are similar to those seen for endovascular treatment adjuvant to surgical evacuation. However, when routinely using endovascular treatment as an adjunctive, the increased complication rate by having two separate procedures may potentially outweigh any benefit of the combined treatments.

A minimally invasive treatment with reduced recurrence risk and comparable complication rates has however the potential for paradigm shift in the treatment of cSDH. Not within the scope of this trial, but eMMA has also been associated with a reduction in healthcare costs, the primary driver being fewer treatments needed [20]. A drawback of the endovascular treatment is that resolution of the hematoma is slower than prompt neurosurgical evacuation. Limited data on timing of clinical improvement with upfront eMMA is currently available. In our experience, a delay of clinical and radiological improvement of 5–10 days and 4–6 weeks respectively can be expected.

Internationally, treatment strategies for bilateral cSDH varies significantly, and reoperation rates for this group seem to be somewhat higher than unilateral cSDH, either by ipsilateral recurrence or opportunistic expansion of the unoperated side [21]. For bilateral cSDH randomized to neurosurgery and unilaterally evacuated at index procedure, additional analysis including subsequent operative treatment on the contralateral side will be performed.

When designing this trial, we have striven to follow clinical routine care as much as possible to facilitate transferal into clinical routine care, should the results be positive.

The trial is academically driven and locally funded by the collaborating efforts of the Neurosurgery and Interventional Neuroradiology departments at Skåne University Hospital. Sponsor is Region Skåne, the publicly funded healthcare provider for the south region of Sweden.

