#### Intervention description {11a}

##### Intervention

Physicians performing the intervention are neuroradiologists with several years of experience in the endovascular field. The procedure is performed under sterile conditions in the angio suite, most commonly under conscious sedation.

Using standard endovascular techniques, arterial access is achieved in the femoral or radial artery. A guiding catheter is advanced to the common (CCA) and external (ECA) carotid arteries of the affected side(s) for baseline angiographic controls and anatomical delineation. A microcatheter is then used for super selective controls of the middle meningeal artery (MMA) for detailed anatomical delineation and then further advanced to a wedged treatment position in an appropriate MMA branch. In preparation, an intra-arterial vasodilating agent, a small dose of local anesthetic, and lastly DMSO are infused in the microcatheter. Under fluoroscopic control, the vessel is embolized with liquid embolysate (Onyx™ or Squid™ or Phil™) until no antegrade flow can be visualized. The process is repeated depending on the number of MMA branches to be treated. Post treatment control angiograms are performed in the ECA and CCA, and arterial access site is closed. An NCCT is performed in the angiolab, and the patient is transferred to neurointensive care unit (NICU) for postoperative controls. Estimated time from vascular access to closure is approximately 1–2 h depending on number of branches and sides to be treated.

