##### Control

Neurosurgical hematoma evacuation is a clinical routine treatment performed under sterile conditions in the operating theatre for cSDH. Most commonly, the procedure is performed under local anesthesia and conscious sedation. Depending on patient cooperability, general anesthesia may be indicated. In case of bilateral hematomas in need of simultaneous evacuation, the procedure is performed under general anesthesia. Antibiotic prophylaxis is given preoperatively.

Hair is removed, and a skin incision is made over the parietal or frontal bone (most often), and 1–3 burr holes are made in the skull and conjoined to form a minicraniotomy. The dura is coagulated and incised. The hematoma membrane is punctured when necessary and the hematoma irrigated using a catheter and fluid at room temperature. After evacuation, a small catheter is left in either the subdural space or under the galea, connected to a uribag for either closed, passive (subdural), or active (subgaleal) drainage. The head is slightly elevated, and the cavity is filled with fluid. Subcutaneous sutures secure the galea and subcutis and staples or sutures close the skin incision.

The patient is transferred to the NICU for 4 h of postoperative controls, or possibly overnight, if necessary. Estimated time from skin incision to wound closure is 30 min–1 h. Drainage is left in place for 24 h and then removed. Skin staples are removed after 7–14 days.

In cases of bilateral hematomas, the most expansive side is usually treated first, and the patient is followed clinically and radiologically to ascertain whether contralateral treatment is needed.

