#### Outcomes {12}

Primary outcome measure:

The primary outcome is the difference in reoperation frequency within 3 months between the two groups. Reoperation is defined as any operative (surgical or endovascular) treatment regarding cSDH on the previously treated side(s).

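### The additional bilateral analysis extends event counting to the untreated side in the neurosurgery arm only, and is even-handed only if every bilateral embolization patient has both sides embolized

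*Protocol article*

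**What the plan says.** Four places in the protocol article bear on this.

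- **Outcomes {12}** ties the primary event to the side already treated ("Reoperation is defined as any operative (surgical or endovascular) treatment regarding cSDH on the previously treated side(s").
- **Control** describes both one-sided and two-sided surgery for bilateral disease. For the first, "the most expansive side is usually treated first, and the patient is followed clinically and radiologically to ascertain whether contralateral treatment is needed". For the second, "In case of bilateral hematomas in need of simultaneous evacuation, the procedure is performed under general anesthesia".
- **Intervention** describes access to the carotid arteries on whichever sides are affected ("A guiding catheter is advanced to the common (CCA) and external (ECA) carotid arteries of the affected side(s") and gives a procedure time of "approximately 1–2 h depending on number of branches and sides to be treated". It neither requires both sides to be embolized in bilateral disease nor describes a staged approach.
- **Discussion** adds the supplementary analysis: "For bilateral cSDH randomized to neurosurgery and unilaterally evacuated at index procedure, additional analysis including subsequent operative treatment on the contralateral side". It gives no counterpart for the embolization arm, attaches no test or significance level, and does not say whether the result is a between-arm comparison or a description of the control patients.

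Bilateral hematoma is eligible under the inclusion criteria. The expected share of bilateral patients is not given.

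**The concern.** The primary definition leaves out a later operation on the second side of a bilateral patient whose first procedure was one-sided. The Discussion brings those operations back in, but only for patients randomized to neurosurgery. Under that rule the control rate can stay the same or rise and the embolization rate cannot change, so any movement is in the direction of the trial's hypothesis.

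Two features make this awkward. First, the subset depends on how the surgeon chose to operate, which is known only after randomization and only in one arm, so it has no randomized comparator. Second, a bilateral patient embolized on one side who later needs the other side treated has the same kind of event, and it is counted nowhere.

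The Discussion itself says that reoperation seems somewhat more frequent in bilateral disease, so readers are likely to look at this result. If it is set beside the primary comparison, part of the difference could come from the counting rule.

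**Working it through.** **The plan's own figure.** Sample size {14} gives 17% versus 6.5%, a two-sided likelihood ratio test, alpha 0.05, power 80%, and 144 per arm. With H(p) = p ln p + (1−p) ln(1−p) and mean proportion 0.1175, the noncentrality per patient per arm is 2[H(0.17) + H(0.065) − 2H(0.1175)] = 0.05487. Power of 80% on 1 df needs 7.849, and 7.849 / 0.05487 = 143.06, so 144 per arm and 288 in total (power 80.3%). The stated size reproduces, and the additional analysis does not enter it.

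**What the one-arm addition does to the planning rates.** Assumptions, none of them in the documents: bilateral share b = 15–25%; share of bilateral controls evacuated on one side u = 50–100%; contralateral operation risk c = 10–20%, independent of ipsilateral reoperation. The added control rate is b × u × c × (1 − 0.17):

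- low: 0.15 × 0.5 × 0.10 × 0.83 = 0.6 points
- high: 0.25 × 1.0 × 0.20 × 0.83 = 4.2 points

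Control moves from 17% to 17.6–21.2%, embolization stays at 6.5%, and the difference goes from 10.5 to 11.1–14.7 points. This shows direction and size, but not yet bias.

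**Is the movement a bias?** Take a case with no treatment effect: each hematoma side carries the same assumed operation risk r = 12% in both arms, treated or not, and the sides are independent. The risk on either of two sides is 1 − 0.88² = 0.2256, which exceeds the one-side risk by d = 0.2256 − 0.12 = 0.1056. Let v be the share of bilateral embolization patients embolized on one side. Then, as control minus embolization:

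- primary definition: b × (v − u) × d
- additional analysis (second side added in control only): b × v × d
- either side counted in both arms: 0

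With u = 100% and b = 15–25%, in percentage points:

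| Embolized on one side (v) | Primary | Additional, as written | Either side, both arms |
|---|---|---|---|
| none | −1.6 to −2.6 | 0.0 | 0.0 |
| half | −0.8 to −1.3 | +0.8 to +1.3 | 0.0 |
| all | 0.0 | +1.6 to +2.6 | 0.0 |

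For example, with b = 0.15 and v = 0.5 the additional analysis gives 0.15 × 0.5 × 0.1056 = 0.0079. The value of u changes the primary column but not the additional one, because after the addition every bilateral control patient is counted on both sides. The additional analysis is neutral at v = 0 and favours embolization for any v above 0; it never favours control.

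**The case against.** The strongest reply is that the one-arm rule corrects an imbalance. The Intervention section speaks of the affected side or sides, and treating one side first is described only under Control. A natural reading is that bilateral embolization patients usually have both sides treated and bilateral surgical patients usually one. The primary definition then exposes two sides to a countable event under embolization and one under control, which favours control, and the Discussion's addition removes that. The first row of the table bears this out. The remark about the number of sides concerns procedure time and would vary anyway, since unilateral and bilateral patients both enter.

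This reply stands in part. It rules out two stronger conclusions that a reader might draw:

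- *That the analysis can never be a neutral check and inflates false-positive findings.* Simulation with no true effect can take the chance of a significant result favouring embolization from about 2.5% to about 6% or 12%. That rests on an assumed 10% event rate per arm, 20% bilateral, 80% treated on one side, a 10% or 20% contralateral rate, and the same one-sided practice in both arms. The documents support none of these inputs and attach no test to this analysis.
- *That it counts routine second-stage surgery as failure.* The Control section makes the second side contingent on follow-up and has a separate route for simultaneous evacuation. The Discussion names expansion of the unoperated side as the mechanism.

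What the reply does not remove is the condition. The protocol nowhere requires both sides to be embolized, so neutrality rests on a practice left open. Nor is this detail left to an analysis plan, because the article states the one-arm rule itself.

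**Conclusion.** The point holds in a limited, conditional form. As written, the additional analysis extends counting in one arm, in a subset formed after randomization. It is even-handed only if every bilateral embolization patient has both sides embolized; otherwise it favours embolization. Under the assumptions above (12% per side, independent sides, 15–25% bilateral, all such controls evacuated on one side) the artefact is +0.8 to +1.3 points if half are embolized on one side and +1.6 to +2.6 if all are. These sizes are illustrations, since the documents give none of the inputs.

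The primary analysis and the sample size of 288 are untouched. The protocol does not call this a sensitivity or robustness analysis, and it may be meant only as a description of the control patients. Severity is minor.

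**What to change.** Replace the Discussion sentence with one rule for both arms, for example: *In an additional analysis of patients with bilateral cSDH at baseline, in both arms, any cSDH operation on either side within 3 months is counted, whatever side or sides were treated at the index procedure. Operations that are the first treatment of a previously untreated side are shown separately in both arms.*

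This defines the group before randomization and gives equal counting however many sides are embolized, so it keeps the correction that the one-arm rule may have been meant to supply. It asks for no change in how many sides are treated. If the analysis is meant only to describe control patients, the protocol should say so.

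The cost is one sentence and one extra table. The side of each operation is already needed for the primary outcome, and bilateral status is known from the baseline scan. The sponsor should accept that the difference between arms may come out smaller than under the one-arm rule.

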## Trial status

Recruitment commenced on March 21, 2022. Approximate completion of final recruitment is expected to first quarter of 2025.

Protocol version 1.0, 2022–02-03.

## Data Availability

Trial investigators at all sites will have access to the final, pseudonymized completed data set. Approval for data analysis for manuscript preparation will be given by the trial core investigative team.

## Abbreviations

AE: Adverse event
CCA: Common carotid artery
CRF: Case report form
CRO: Contract research organization
cSDH: Chronic subdural hematoma
DMSO: Dimethyl sulfoxide
DSMB: Data safety monitoring board
EC: Ethical committee
ECA: External carotid artery
eCRF: Electronic case report form
eMMA: Embolization of middle meningeal artery
GCP: Good Clinical Practice
GDPR: General Data Protection Regulation
ICH: International Council for Harmonisation
ICMJE: International Committee of Medical Journal Editors
MMA: Middle meningeal artery
MRI: Magnetic resonance imaging
mRS: Modified Rankin scale
mSv: Millisievert
NCCT: Non contrast-enhanced computerized tomography
NICU: Neurointensive care unit
PI: Principal investigator
RCT: Randomized controlled trial
SAE: Serious adverse event
SOP: Standard operating procedure
VAS: Visual analog scale
